## Abstract

**Background:**

Xerostomia is a common side effect of radiotherapy in patients with head and neck tumors that negatively affects quality of life. There is no known effective standard treatment for xerostomia. Here, we present the study protocol used to evaluate the safety and preliminary efficacy of allogeneic mesenchymal stromal stem cells (MSCs) derived from umbilical cord tissue.

**Patients and methods:**

Ten oropharyngeal cancer patients with post-radiation xerostomia and no evidence of disease recurrence 2 or more years after (chemo)irradiation (intervention group) and 10 healthy volunteers (control group) will be enrolled in this nonrandomized, open-label, phase I exploratory study. MSCs from umbilical cord tissue will be inserted under ultrasound guidance into both parotid glands and both submandibular glands of the patients. Toxicity of the procedure will be assessed according to CTCAE v5.0 criteria at days 0, 1, 5, 28, and 120. Efficacy will be assessed by measuring salivary flow and analyzing its composition, scintigraphic evaluation of MSC grafting, retention, and migration, and questionnaires measuring subjective xerostomia and quality of life. In addition, the radiological, functional, and morphological characteristics of the salivary tissue will be assessed before, at 4 weeks, and at 4 months after the procedure. In the control group subjects, only salivary flow rate and salivary composition will be determined.

**Discussion:**

The use of allogeneic MSCs from umbilical cord tissue represents an innovative approach for the treatment of xerostomia after radiation. Due to the noninvasive collection procedure, flexibility of cryobanking, and biological advantages, xerostomia therapy using allogeneic MSCs from umbilical cord tissue may have an advantage over other similar therapies.

## Introduction

### Xerostomia in patients with head and neck cancer

Radiotherapy (RT) is one of the main therapeutic modalities for head and neck cancer (HNC): approximately 80% of patients diagnosed with this cancer undergo RT.^1^ Unfortunately, RT is associated with significant toxicity in the head and neck region. While the acute side effects of RT usually occur within 90 days of treatment initiation, the toxic late effects can occur months or even years after treatment completion. Acute side effects occur most frequently in tissues with high proliferation activity, and pathological mechanisms include radiation-induced death of stem cells with the subsequent inflammatory response. Healing and regeneration of the tissue depends on the survival of the remaining stem cells at the site of injury or on their migration from the surrounding tissue, which is less irradiated or not irradiated at all, to the damaged area.^2^ In the head and neck region, the most common RT-related acute side effects include radiodermatitis and radiomucositis, affecting approximately 80% of patients. They also frequently suffer from dysgeusia, dysphagia, and xerostomia, i.e., a feeling of dry mouth due to saliva deficiency or changes in saliva composition.^3^

The first symptoms of salivary deficiency may manifest after the first irradiation fractions and often progress to a chronic condition, especially when the average dose received by the major salivary glands, such as the parotid glands, reaches or exceeds 26 Gy or, in the case of the submandibular glands, 35 Gy.^4^ Unfortunately, despite various improvements and advances, prevention of xerostomia remains a challenge. Modern radiation techniques, such as intensity-modulated radiotherapy, the use of proton or heavy ion beams, allow efficient, although not complete, sparing of the healthy tissue around the tumor.^5,6^ Careful oral hygiene, regular rinsing of the mouth, adequate hydration, and the use of intraoral stents that separate healthy tissue from the tumor are among the generally recommended preventive measures.^7^ The use of amifostine, a free radical scavenger, with its questionable long-term efficacy and side effects occurring in nearly half of patients, remains the subject of professional debate.^8^ Surgical relocation of the submandibular gland contralateral to the tumor to the nonirradiated submental area is an invasive procedure and only suitable for a limited number of HNC patients.^9^

Various synthetic saliva substitutes based on methylcellulose are used to relieve the sensation of dry mouth, but with very variable effects in patients. The same is true for acupuncture, electrical nerve stimulation, and hyperbaric oxygenation.^10^ If salivary gland function is partially preserved, cholinergic analogs (e.g., pilocarpine) can be used to stimulate saliva production, but they are rarely used in practice because of numerous side effects.^10^

Because they do not target regeneration of damaged glandular tissue, existing preventive and therapeutic approaches for newly diagnosed HNC patients or for patients with previously developed radiation-induced salivary gland hypofunction are limited and of questionable efficacy. As mentioned above, the pathophysiology of these complications is multifactorial and includes acute and late processes that may persist for several years after RT. They are characterized by chronic inflammation, development of fibrosis, loss of local stem and progenitor cells, and deterioration of survival conditions for the remaining acinar cells.^4^ Consequently, salivary gland hypofunction and resulting xerostomia remain the most common long-term side effects of RT in HNC patients, which usually has a strong negative impact on their quality of life.^11^

### Mesenchymal stromal stem cells

Mesenchymal stromal stem cells (MSCs) originate from the mesodermal layer from which various mesenchymal tissues develop during embryonic development. In adults, MSCs represent a heterogeneous cell population that includes multipotent MSCs that can differentiate into cartilage, bone, and fat cells. Because of their regenerative capabilities, they are often referred to as “adult stem cells” and are frequently studied in the field of regenerative medicine.^12^ The most common biological sources for MSC production are bone marrow, adipose tissue, umbilical cord tissue, and others. The production and cultivation of MSCs is a relatively straightforward and safe process without significant ethical concerns. MSCs are characterized by low or no expression of major histocompatibility complex molecules, making them suitable for an allogeneic setting. Another phenotypic feature is the simultaneous expression of several markers, including CD73, CD90, and CD105, and the lack of expression of hematopoietic markers such as CD45.^13^

Although a specific subset of MSCs can differentiate into different cell types, there is increasing evidence that the main therapeutic effects of MSCs are mediated by paracrine mechanisms involving the secretion of various active biomolecules. Factors secreted by MSCs may have angiogenic, anti-apoptotic, regenerative, and immunomodulatory effects.^14^ Among all types of stem cells, MSCs possess a unique immunomodulatory effect. Their activity is based on the expression of immunomodulatory enzymes such as indoleamine 2,3-dioxygenase (IDO) and inducible nitric oxide synthase (iNOS), immunosuppressive biomolecules such as prostaglandin E2 (PGE2) and hepatocyte growth factor (HGF), the production of immunosuppressive cytokines such as interleukin (IL)-10 and transforming growth factor (TGF)-β, or the expression of inhibitory surface molecules such as HLA-G and programmed death ligands PD -L1 and PD -L2. With such an extensive repertoire of immunomodulatory mechanisms, MSCs can regulate the function of different types of immune cells belonging to both innate and adaptive immunity. These include monocytes/macrophages as well as important antigen-presenting cells such as dendritic cells (DCs). MSCs can also suppress the activity of T and B lymphocytes, natural killer (NK) cells, neutrophils, and mast cells. On the other hand, MSCs have been shown to promote the generation of regulatory immune cells such as regulatory T cells (Tregs), tolerogenic DCs, and myeloid-derived suppressor cells.^15^ MSCs markedly inhibit T cell proliferation both in an allogeneic setting and upon exposure to various mitogens.^16,17^ In co-cultures with helper Th1-type T cells, MSCs can greatly reduce the secretion of pro-inflammatory cytokines (e.g., IFN-γ and TNF-α) and increase the proportion of T cells producing anti-inflammatory cytokines (e.g., IL −10), such as Tr1 cells.^18^ They may also inhibit the activation of CD8+ cytotoxic T cells, resulting in a decreased response to alloantigens and decreased antigen-specific lysis of allogeneic cells.^19,20^ In summary, MSCs can suppress immune activation and promote a tissue regeneration through mechanisms involving the production/expression of various cell-bound and soluble factors.

An important issue in the clinical translation of MSC-based advanced therapy medicinal products (ATMPs) is the known heterogeneity of MSC preparations used in clinical trials. Variations in final product formulations may result from donor variability, tissue source variability, frequent and extensive cell passage variability during manufacturing, and variable use of fresh or directly thawed cryopreserved MSCs, the suboptimal functionality of which has been reported.^21,22^ In the present study, we will address these issues by introducing a novel protocol for the preparation of MSCs that allows for equivalent final product formulations for each recruited patient by using only freshly cultured cells with very low passages (p ≤ 2) and high viability, as described below.

Advanced therapy medicinal products based on MSCs also represent an interesting and novel therapeutic option for patients with radiation-induced salivary gland damage and existing xerostomia because they act through different mechanisms that have both immunomodulatory and regenerative effects.^23^ Since xerostomia significantly limits patients’ quality of life, exploring the potential efficacy of MSC-based therapy is of high priority and with direct clinical relevance.^11^

## Methods and design

The study is being conducted at the Institute of Oncology Ljubljana in collaboration with the Slovenian Institute for Transfusion Medicine, the Clinic of Nuclear Medicine at the University Medical Centre Ljubljana, and the Institute of Biochemistry and Molecular Genetics at the Faculty of Medicine, University of Ljubljana. It is a non-randomized, single-center, open-label, phase I exploratory study. The study will include 10 patients (intervention group) and 10 healthy volunteers (control group) (Figure 1).

**FIGURE 1. j_raon-2023-0052_fig_001:**
[figure not shown]
Design of the clinical trial. CTCAE v5 = Common Terminology Criteria for Adverse Events version 5.0; MRI = magnetic resonance imaging; MSC = allogeneic mesenchymal stromal stem cells; RT = radiotherapy; SCC = squamous cell carcinoma; US = ultrasound; [99mTc]*HMPAO* = Technetium 99m-hexamethylpropyleneamine oxime; [99mTc]TcO_4_ = Technetium 99m-pertechnetate

The aim of the study is to evaluate the safety and preliminary efficacy of treatment of xerostomia after irradiation with allogeneic MSC from umbilical cord tissue. Thus, we hypothesize that the treatment of post-radiation xerostomia with allogeneic MSC from umbilical cord tissue is safe and effective.

The study protocol was approved by the National Medical Ethics Committee (No. 0120-193/2023/3) and registered in the ClinicalTrial.gov database (NCT06012604) under the title: “*Treatment of Post-radiation Xerostomia with Allogeneic Mesenchymal Stromal Stem Cells: A Pilot Study”,* registered on 22 August 2023; https://classic.clinicaltrials.gov/ct2/show/NCT06012604

### Objectives

The primary objective of the study is to evaluate the safety of administering allogeneic MSCs to the submandibular and parotid glands of patients with radiation-induced salivary gland dysfunction and xerostomia, with a 4-month follow-up after the procedure.

Secondary objectives of the study include evaluation of the efficacy of the procedure and radiologic, functional, and morphologic changes in glandular tissue after application of allogeneic MSC (Table 1).

**TABLE 1. j_raon-2023-0052_tab_001:** Primary and secondary objectives of the study

**Objective**	**Definition of objective**	**Time of evaluation**
**Primary**		
Evaluation of the safety of administration of allogeneic MSCs	Adverse event assessment (CTCAE v.5 criteria): pain at application site, mouth sensation, infection	From the start of therapy to the last follow-up (days 1, 5, 28, and 120)
**Secondary**		
Efficacy of the procedure	Measurement of unstimulated/stimulated salivary flow and saliva composition	During recruitment, day 28 and 120 post-procedure
	Assessment of subjective degree of xerostomia (questionnaires)	During recruitment, days 28 and 120 after the procedure
		Immediately after the procedure (day 0)
	Scintigraphic evaluation of grafting, retention, and migration of allogeneic MSCs	During recruitment, on days 28 and 120 after the procedure
	Assessment of patients’ quality of life	
Radiological changes of the salivary tissue	Magnetic resonance imaging (MRI): volume, signal, and diffusivity changes	During recruitment, on days 28 and 120 after procedure
	Ultrasonography (US): consistency (firmness)	
Functional changes of the salivary tissue	Scintigraphy with ([99mTc]TcO_4_^−^ (pertechnetate): uptake of radioisotope in parenchyma, ejection fraction	During recruitment, on days 28 and 120 after procedure
Morphological changes of the salivary tissue	Core needle biopsy specimens: composition, inflammatory infiltrate, metaplasia, reactive changes	During recruitment, on day 120 after the procedure

CTCAE v.5 = Common Terminology Criteria for Adverse Events version 5.0; MSCs = allogeneic mesenchymal stromal stem cells

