#### Scintigraphy with [99mTc]Tc-HMPAO-labeled MSCs.

One hour and twenty-four hours (the next day) after MSC application, planar head and whole-body images and SPECT/CT images of the head will be performed to assess the distribution, retention, and migration of MSCs from the application site.

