#### Scintigraphy with *[99mTc]TcO_4_^−^*

Before and 4 months after MSC transplantation, scintigraphy of the salivary glands will be performed with the radiopharmaceutical pertechnetate (*[99mTc]TcO_4_^−^*). After intravenous administration, the radiopharmaceutical accumulates in the functioning parenchyma of the salivary glands and is subsequently excreted into the oral cavity after stimulation with citric acid. After administration of the radiopharmaceutical, a 10-minute planar head recording will be made, followed by oral administration and stimulation of the salivary glands with citric acid and another 10-minute planar recording. In this study, the uptake of the radiopharmaceutical in the functioning parenchyma and the excretory fraction of each gland will be evaluated qualitatively and semiquantitatively. Both parameters, determined before and after MSC transplantation will be compared.

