## Intervention

MSC-based investigational medicinal products (IMPs) will be prepared at the Slovenian Institute for Transfusion Medicine according to validated standard operating procedures approved by the National Medical Ethics Committee (No. 0120-60/2018/7, 24.4.2018). The umbilical cord tissue will be used as the primary biological source. The tissue is first seeded in an *ex vivo* culture. After the first 10–14 days (passage 0), adherent cells begin to proliferate extensively and reach adequate confluence within the next 7 days. They are then harvested in passage 0 and reseeded for further cell expansion (passage 1). At the end of passage 1, cells from 4 different donors are harvested and pooled into a single cell suspension in equal ratios. They are then redistributed into identical aliquots and cryopreserved as “off-the-shelf units” (EQ-MSC) available for “per patient” orders. For each patient, an identical aliquot of EQ-MSCs is thawed and seeded in cell culture for 3–5 days prior to the procedure (passage 2) to achieve optimal numbers and cell fitness for the final product. The final drug formulation will be prepared as a suspension of 50×10^6^ MSCs/ml in a physiological solution with an addition of 0.5% human albumin. It will be filled in syringes of 0.5 ml or 1.0 ml with a 23G 0.6×25 mm hypodermic needle.

In the intervention group, each patient will receive an ultrasound-guided injection of 50×10^6^ MSCs into each parotid gland and an injection of 25×10^6^ MSCs into each submandibular gland, without anesthesia. To ensure even distribution of the MSC suspension, each parotid gland will receive injections in two areas: the tail and the body of the gland.

Approximately 5% of the volume of the prepared MSC injectate will be removed under aseptic conditions. The cells will be labeled with hexamethylpropyleneamine oxime ([99mTc]Tc-HMPAO) and resuspended with the remaining injection material for administration to the patient.

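### Labelled-cell scans at 1 and 24 hours show where the label lies on the first day; they cannot show grafting and are not an efficacy measure

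*Protocol article*

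**What the plan says.** The Abstract (Patients and methods) names "scintigraphic evaluation of MSC grafting, retention, and migration" as one of the ways efficacy will be assessed. Table 1 repeats this among the secondary objectives, under efficacy of the procedure: "Scintigraphic evaluation of grafting, retention, and migration of allogeneic MSCs".

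The section on scintigraphy with HMPAO-labelled cells fixes the images at "One hour and twenty-four hours (the next day) after MSC application" and gives their purpose as "to assess the distribution, retention, and migration of MSCs from the application site". Grafting does not appear there.

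The Intervention section describes the labelling: "Approximately 5% of the volume of the prepared MSC injectate will be removed under aseptic conditions", and then "The cells will be labeled with hexamethylpropyleneamine oxime ([99mTc]Tc-HMPAO) and resuspended with the remaining injection material".

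The timing differs between places. Table 3 marks the labelled-cell scan on day 0 only. In the extracted Table 1 the time column is shifted by a line, but its entry "Immediately after the procedure (day 0" fits no other measure. The imaging section adds a scan on the next day.

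A separate test, scintigraphy with intravenous pertechnetate, measures gland function before the procedure and at 4 months. In that section the protocol states that "the radiopharmaceutical accumulates in the functioning parenchyma of the salivary glands".

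**The concern.** The stated objective is larger than the measurement. Grafting means that cells survive and persist in the tissue. A label image one day after injection cannot establish that, and the imaging section itself does not claim it.

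Filing the scan under efficacy adds to the problem. The Discussion says that the nuclear medicine studies are meant to help define the effect of the therapy, so an effect reading is foreseeable. The authors also present this as the first use of umbilical-cord MSCs for xerostomia and intend the results to inform the next trials. A statement that the cells grafted, resting on label position at 24 hours, could mislead those designs.

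A second and weaker issue concerns what the signal represents. The camera sees technetium, not living cells. The injected organs are the ones in which, by the protocol's own account, pertechnetate accumulates. If some label left the cells in that form, location alone would not separate it from label still inside cells.

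**Working it through.** The plan gives no figure of its own on this point, so there is none to reproduce. The check sets the objective beside the measurement and then sizes the two limits.

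**1. Objective against measurement**

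| Place | What is to be assessed | When |
|---|---|---|
| Abstract | grafting, retention, migration, as efficacy | not given |
| Table 1 | the same, as efficacy | day 0 |
| Table 3 | labelled-cell scan | day 0 only |
| Imaging section | distribution, retention, migration | 1 h and 24 h |
| Discussion | treatment effect | 4 weeks and 4 months |

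No labelled-cell image is planned after 24 hours. The introduction to MSCs also says that their main therapeutic effects are thought to be paracrine, so even correctly located cells would not by themselves be a benefit.

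**2. How far the label can reach**

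The remaining share is 2^(−t/T). The documents give no half-life, so T = 6 h is an assumption, with a range of 5.5 to 6.5 h.

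- 1 h: 2^(−1/6) = 0.891 (0.882 to 0.899)
- 24 h: 2^(−24/6) = 0.0625 (0.049 to 0.077)
- Day 5: 2^(−120/6) = 9.5 × 10⁻⁷ (2.7 × 10⁻⁷ to 2.8 × 10⁻⁶)
- Day 28: 2^(−672/6), about 2 × 10⁻³⁴, effectively nil; day 120 likewise

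The ratio of 24 h to 1 h from decay alone is 0.0625/0.891 = 0.070 (0.055 to 0.086). This is a known factor and can be corrected. Decay is therefore not the fault at 24 hours, but it does mean that this label cannot follow cells to any efficacy visit.

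**3. Labelled cells**

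The Intervention section gives 50 million cells per parotid and 25 million per submandibular gland.

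- Total: 2 × 50 + 2 × 25 = 150 million
- Labelled: 0.05 × 150 = 7.5 million
- Per parotid: 0.05 × 50 = 2.5 million; per submandibular gland: 0.05 × 25 = 1.25 million

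**4. Possible signal from free label (illustration only)**

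Let r be the share of label truly retained in cells in the glands, p the share of the remaining label that becomes pertechnetate, and u the share of that pertechnetate taken up by the four glands. The apparent decay-corrected retention is r + (1 − r)pu. The documents give neither p nor u. The assumed ranges are p = 10 to 100% and u = 0.5 to 5%.

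- r = 0: from 0.1 × 0.005 = 0.05% to 1 × 0.05 = 5%
- r = 20%: from 0.20 + 0.80 × 0.0005 = 20.0% to 0.20 + 0.80 × 0.05 = 24.0%

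Within these assumptions the false signal is small. If 10 to 40% of the label detached, which is also an assumption, that whole share would be misplaced only if all of it were pertechnetate and all of it went to the glands. That is a ceiling, not an expected size.

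**The case against.** The strongest reply is that this is loose wording in a condensed article. The imaging section already omits grafting. The scan is one part of a secondary objective in a 10-patient exploratory phase I study whose primary objective is safety, and no test or sample size depends on it. Decay correction, checks of label stability and regions of interest commonly sit in a full protocol or imaging manual. Early retention and migration of the label are fair targets for planar, whole-body and SPECT/CT images over 24 hours.

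Most of this stands. It limits the consequence, excludes any complaint about missing imaging detail, and means that retention and migration should stay in the objective. It does not remove the mismatch, because the article itself fixes both the objective and the scan times.

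A reader might go further and infer that the scans will show retention where no cells remain, that the error favours the product, or that better-functioning glands will falsely seem to keep more cells and so create a spurious link with response. The documents do not support this:

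- Nothing in them says that the HMPAO label leaves these cells, how much leaves, or in what chemical form.
- The statement on gland uptake concerns intravenous pertechnetate in functioning parenchyma. The enrolled glands have received mean doses above 26 Gy (parotid) or 35 Gy (submandibular), and unstimulated flow is 0.05 to 0.20 ml/min. Uptake may be low, though it is not shown to be nil.
- No analysis relating retention to response is planned.

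**Conclusion.** The concern holds for the wording and classification of the objective. Label images at 1 and 24 hours can describe early distribution, retention and migration of the label. They cannot show engraftment, and they are not evidence of efficacy at 4 weeks or 4 months. This rests on the article's own scan times and needs no outside figure; the decay numbers, under the assumed half-life, only confirm that the label cannot reach those visits. Day 0 in Tables 1 and 3 also does not cover the next-day scan, subject to the shifted rows in the extracted Table 1.

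Confounding by free pertechnetate is a conditional risk of unknown size. The 0.05 to 5% illustration rests wholly on assumed values and should not be cited as an estimate.

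The consequence is limited, because the measure is secondary and exploratory. The point is still worth correcting before results are reported, since an engraftment claim would go beyond the data.

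**What to change.** - In the Abstract and Table 1, replace the objective by *early distribution, retention and migration of the label up to 24 h*.
- List it as biodistribution rather than efficacy, and state that no engraftment claim will be made from it.
- Align the day 0 timing in Tables 1 and 3 with the next-day scan in the imaging section.
- Report, for each gland, decay-corrected activity at 24 h relative to 1 h: (A₂₄/A₁) × 2^(23/T). Show it next to that gland's baseline pertechnetate uptake, which is already measured.
- Inspect the planned whole-body images for signs of free label.

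The first three are changes of wording. The last two use images already scheduled and add no scan or patient visit. The cost is some extra image analysis and a more modest claim.
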